### **9.3 Adverse Event Monitoring**

#### **Local Safety Monitor and Data Monitoring & Ethics Committee**

The Local Safety Monitor (LSM), [name], will provide real-time safety oversight. The LSM will review SAEs immediately after they occur and follow the events until resolution. The LSM has the power to suspend enrolment into the study if deemed necessary following an SAE and convene a meeting with the Sponsor and Principal Investigator immediately. The LSM can convene a meeting with the Sponsor, PI or other parties involved at any time for further discussion as necessary.

An independent Data Monitoring & Ethics Committee (DMEC) will be set up prior to initiating the trial. The DMEC will be appointed to review relevant safety information and all Serious Adverse Events. Immunogenicity data will also be provided to the DMEC. A detailed description of DMEC procedures is provided in the DMEC charter.

#### **Methods and Timing for Assessing, Recording, and Analyzing Safety Parameters**

The following scale will be used to assess the severity of all AEs:

- 0 = Absence of the indicated symptom
- 1 = Mild (awareness of a symptom but the symptom is easily tolerated)
- 2 = Moderate (discomfort enough to cause interference with usual activity)

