**6.1 Laboratory Tests**

**Haematology** Full blood count (FBC) including platelet count

**Biochemistry** Creatinine, alanine transaminase (ALT), alkaline phosphatase (ALP), bilirubin

**MVA.HIVA immunogenicity** Frequency of IFN- $\gamma$  producing cells using ex-vivo and cultured ELISPOT assays after overnight stimulation with pools of 15-mer peptides overlapping by 11 amino acids spanning the length of antigen HIVA.

**EPI immunogenicity** Measurement of vaccine-induced antibody levels to DTwP, Hib, HepB, PCV-7 and OPV.

**Table 7.** Temporal course of infant blood investigations

| Investigation           | Wk 19 | Wk 21 | Wk 28 | Wk 36 |
|-------------------------|-------|-------|-------|-------|
| Haematology             | X     | X     | X     |       |
| Biochemistry            | X     | X     | X     |       |
| MVA.HIVA Immunogenicity | X     | X     | X     | X     |
| EPI Immunogenicity      | X     | X     |       |       |
| HIV test                |       |       | X     |       |
| HLA typing              |       |       |       | X     |

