## **CONFIDENTIAL**

clinically significant. The following laboratory parameters will be monitored during the course of this study (as previously outlined): full blood count (FBC), creatinine and ALT.

Expected local reactions to the vaccine will not be recorded as an adverse event, but will be recorded on the CRFs. These include:

- Redness
- Induration
- Scaling / Blistering / Ulceration
- Axillary lymph node enlargement
- Pain (scored as follows)
  - 0 No pain
  - 1 Painful to touch
  - 2 Partial restriction of activities
  - 3 Unable to use the arm

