## **CONFIDENTIAL**

- 3 = Severe (incapacitating; unable to perform usual activities; requires absenteeism or bed rest)
- 4 = Life-threatening

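### The single symptom- and function-based severity scale cannot rank asymptomatic laboratory adverse events by size, and some of its anchors do not transfer to infants

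*Protocol*

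**What the plan says.** The severity rule is in Protocol section 9.3, under *Methods and Timing for Assessing, Recording, and Analyzing Safety Parameters*. Its scope is universal: "The following scale will be used to assess the severity of all AEs". There are five grades:

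- The lowest turns on having no symptom: "0 = Absence of the indicated symptom".
- The second turns on perceiving one: "1 = Mild (awareness of a symptom but the symptom is easily tolerated".
- The third, labelled moderate, needs discomfort that gets in the way of what the child normally does.
- The fourth turns on incapacity: "3 = Severe (incapacitating; unable to perform usual activities; requires absenteeism or bed rest".
- The highest has no symptom condition: "4 = Life-threatening".

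Section 9.1 gives two alternative routes by which a laboratory change becomes an adverse event: it alters the child's functional status, or the attending physician regards it as clinically significant. It then names the laboratory parameters to be followed, referring back to an earlier outline, as "full blood count (FBC), creatinine and ALT". The earlier outline, section 6.1, lists the biochemistry panel as "Creatinine, alanine transaminase (ALT), alkaline phosphatase (ALP), bilirubin".

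Section 8 makes adverse events, reactogenicity, biochemistry and haematology together the primary safety outcome, and section 11.2.1 compares them between the groups.

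**The concern.** A severity scale has to give each recorded event a grade that reflects how bad it was and that another assessor would also give. Two features of this one work against that.

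First, the scale is tied to symptoms and function, while the definition of an adverse event is wider and takes in laboratory changes without symptoms. Where the two meet, the written rule either gives such an event the grade for absence or gives it no fitting grade short of life-threatening.

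Second, the wording appears to come from an adult scale. Infants here are vaccinated at 20 weeks and followed to 36 weeks. They cannot tell anyone that they are aware of a symptom, and absenteeism has no meaning for them.

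At stake is the severity profile of a first trial of this product in infants, with 24 vaccinated and 24 control children. At that size, a few events graded differently would change the picture. The trial is open in the field (section 4.2, *Masking*, masks only the immunology laboratory), so loosely anchored grades are also exposed to knowledge of allocation.

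**Working it through.** The plan states no figure on this point, so the check sets the grades against the adverse event definition and the population.

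**Inputs.** Grades 0 to 4 and their scope: section 9.3. Routes by which a laboratory change becomes an adverse event: section 9.1. Population and follow-up: section 3 and Table 6. Laboratory schedule: section 6.1 and Table 7. Use of the data: sections 8 and 11.2.1.

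**Step 1: an asymptomatic laboratory change that the physician judges clinically significant, with no change in function.**

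| Grade | What the grade requires | Does this event meet it? |
|---|---|---|
| 0 | no symptom | yes, literally |
| 1 | awareness of a tolerated symptom | no, there is no symptom |
| 2 | discomfort that interferes with activity | no |
| 3 | incapacity or inability to carry on activities | no |
| 4 | threat to life, with no symptom condition | only if the value is judged life-threatening |

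The event therefore has two possible grades, 0 or 4. A modest and a marked rise in ALT, both clinically significant and neither life-threatening, receive the same grade. The document shown gives no laboratory thresholds that would separate them.

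**Step 2: a laboratory change that alters function.** Grades 2 and 3 become available through the functional effect. The gap is therefore specific to the second route in section 9.1.

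**Step 3: a clinical event in an infant of 20 to 36 weeks.**

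- Grade 1: awareness cannot be observed directly. An assessor has to infer it.
- Grade 2: interference with activity can be observed by a parent or clinician, but usual activity is not defined for an infant.
- Grade 3: inability to carry on activities can be observed, with the same lack of definition. Absenteeism and bed rest do not apply.
- Grade 4: can be applied as written.

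Grading is possible, but the boundaries between grades 1, 2 and 3 are left largely to the individual assessor.

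**Step 4: how much data is touched.** Table 7 places haematology and biochemistry after vaccination at weeks 21 and 28. That is 2 scheduled safety draws × 48 infants = 96 draws at most, of which 2 × 24 = 48 are in vaccinated infants. How many would yield an asymptomatic laboratory event cannot be derived from the protocol.

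**Step 5: the analyte lists.** Section 6.1 names four biochemistry tests. The list in section 9.1 names two of them, creatinine and ALT, and omits ALP and bilirubin while claiming to follow the earlier outline. The lists disagree.

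**Step 6: what depends on the grade.** The serious adverse event definition (section 9.1) is based on outcomes. Expedited reporting (section 9.2) turns on seriousness, expectedness and relatedness. The halting rule (section 9.3) is triggered by a SUSAR. Tables 2 and 3 concern serious events. None of these uses the severity grade.

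**The case against.** The strongest reply is that little depends on this scale. No decision rule uses the grade, no severity table is specified, and section 11.2.1 compares haematology and biochemistry directly between groups, so laboratory toxicity would still be visible in the values. All of that stands, and it limits the consequence. It does not mend the rule: severity is recorded for every adverse event within a primary outcome. Laboratory values could be regraded later, but a clinical grade given without a usable anchor cannot be reliably reconstructed.

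A second reply is that grade 0 is the nil entry for a symptom that was asked about, not a grade for an event that exists. That is a natural reading. On it, an asymptomatic laboratory event short of life-threatening has no grade at all, so the gap remains.

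A third is that laboratory grading may be held in operating procedures or case report forms that are not shown. It may be, but section 9.3 assigns this scale to all adverse events, so a different laboratory scale elsewhere would conflict with the protocol as written.

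Some stronger readings are tempting and should be resisted:

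- A reader might infer that every laboratory event scores 0 or 1 whatever its size. Grade 1 needs a symptom, grade 4 does not, and a change affecting function can reach grade 2 or 3.
- A reader might infer that clinical events cannot be graded at all in infants. The activity-based parts of grades 2 and 3 can be observed.
- A reader might take the scale to rest on self-report. The protocol does not say who reports the symptoms or who assigns the grade.
- A reader might conclude that ALP and bilirubin are lost to safety monitoring. The general definition in section 9.1 covers any laboratory variable, and section 11.2.1 compares biochemical data without restriction.

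Expected local reactions are unaffected. Section 9.1 keeps them out of the adverse event record and scores pain separately, with anchors such as use of the arm that can be observed in an infant. That shows suitable anchors were within reach.

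**Conclusion.** The point holds in limited form. Sections 9.1 and 9.3 do not fit together: the first admits asymptomatic laboratory events, and the second gives them only grade 0 or grade 4 unless function changes. Laboratory events therefore cannot be ranked by size. The anchors on awareness and on absenteeism or bed rest do not transfer to infants, so clinical grades 1 to 3 are poorly reproducible in a trial that is open in the field.

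The effect is on the reported severity profile within the primary safety outcome. It does not reach serious event reporting or halting, and it does not hide the laboratory values. The number of events affected cannot be estimated from the document. The mismatch in analyte lists is a minor matter of reconciliation.

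The conclusion assumes that the scale is applied as written and that no separate laboratory grading overrides it. The change is worth making because it is cheap and the clinical grades cannot be reliably repaired afterwards.

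**What to change.** In section 9.3:

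- Replace the anchors that do not transfer with ones that a parent or clinician can observe in an infant, and state what usual activity means at this age. The choice of anchors belongs to the sponsor.
- Take laboratory events out of the symptom scale. Grade them on a separate, prespecified numeric scale based on age-appropriate reference ranges, applied in the same way to both groups.

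In section 9.1, reconcile the list of monitored laboratory parameters with section 6.1, so that the status of ALP and bilirubin is clear.

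The cost is protocol and case report form wording, with no extra visits, blood or staff. The downside is that more laboratory values will carry a non-zero grade and will need to be explained in the report.

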## **CONFIDENTIAL**

- 3 = Severe (incapacitating; unable to perform usual activities; requires absenteeism or bed rest)
- 4 = Life-threatening

### **Procedures to be Followed in the Event of Abnormal Laboratory Test Values or Abnormal Clinical Findings**

Any infant found to have a clinically significant condition prior to inclusion in the study (e.g. heart failure, respiratory distress) or abnormal biochemical or haematological result may have the test repeated to ensure this was not a laboratory error or spurious result. If the test remains clinically significant the infant will be excluded from the study and referred to the appropriate facility (e.g. Royal Victoria Teaching Hospital paediatric clinic) for further investigation and management with the permission of their parents. If occurring during the trial, tests may be repeated to verify the results, and further tests may be instigated to establish causality. If necessary the child will be withdrawn from the study. The infant's parents will be kept informed of all such occurrences and advised of actions to be taken, and their verbal/written consent taken for extra tests where appropriate.

### **Halting Rules**

Any SUSAR will result in suspension of the trial until a safety review is convened. The trial may be discontinued by the Sponsor, the Gambia Government / MRC Joint Ethics Committee or the Oxford Tropical Research Ethical Committee.

The Sponsor delegates to the DMEC the right to temporarily suspend or prematurely discontinue this trial at any time and for any reason as described in the DMEC charter. If the trial is stopped or suspended prematurely, the Sponsor will inform the Principal Investigator. If such action is taken, all effort must be made to ensure the safety of the participants enrolled in the study. The Principal Investigator will inform the relevant ECs about the decision and provide the reason for the suspension or termination.

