**CONFIDENTIAL****4.1 Sample size:**

A total of 48 mother-infant couples will be enrolled into the study and randomized in two groups of 24.

**Group 1:** MVA.HIVA administered at 20 weeks of age (n=24)

**Group 2:** Normal EPI vaccine schedule (control group) (n=24)

This study is a pilot study and the immunogenicity analyses will be mainly descriptive. As such, it is not powered to provide definitive evidence of vaccine-induced effects; rather it is based on smaller numbers of participants and will only indicate trends, feasibility, or size of effect and variability of measurements to inform the design of more definitive studies. The rate of serious adverse events will be used as one measure of the safety of the candidate vaccine. Table 2 shows examples of sample size calculations for safety in terms of the ability to detect SAEs, i.e. the probabilities of observing 0, 1+ (1 or more), 2+ or 3+ SAEs among group of n=24 for a range of possible true event rates. If none of the 24 volunteers receiving the vaccine experiences an SAE definitely related to the vaccine, the 95% two-sided upper confidence bound for the rate of such reactions in the population is 13.8% (Table 3).

**Table 2.** Probabilities of detecting events for n=24

| Event rate (SAE) | Detect. Probability (0 events/24 vol's) | Detect. Probability (1+ events/24 vol's) | Detect. Probability (2+ events/24 vol's) | Detect. Probability (3+ events/24 vol's) |
|------------------|-----------------------------------------|------------------------------------------|------------------------------------------|------------------------------------------|
| 0.010            | 0.88                                    | 0.11                                     | 0.01                                     | <0.01                                    |
| 0.025            | 0.74                                    | 0.26                                     | 0.03                                     | <0.01                                    |
| 0.035            | 0.65                                    | 0.35                                     | 0.06                                     | 0.01                                     |
| 0.050            | 0.54                                    | 0.46                                     | 0.12                                     | 0.02                                     |

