### **Visit 3 – VACCINATION VISIT, MVA.HIVA vaccination day (Infant aged 20 weeks $\pm$ 10 days)**

## CONFIDENTIAL

- Subjects will be brought to the vaccine trial clinic.
- Continued consent to participate in the study will be confirmed.
- Inclusion and exclusion criteria will be checked.
- Results of FBC and biochemistry from previous week will be reviewed by the research physician to ensure the child is eligible for randomisation.
- An interim medical history will be taken.
- Physical examination including vital signs (temperature, respiratory rate, pulse rate), and anthropometry (weight, mid left upper arm circumference (MUAC), length) will be performed by the research field worker / research nurse.
- The screening safety profile will be reviewed by the research physician and those children that fulfill all inclusion criteria and no exclusion criteria will be randomised to one of the two study groups by selecting an envelope containing the block randomized treatment group that they are in:
  - **Group 1** infants will receive MVA.HIVA ( $5 \times 10^7$  pfu in no more than 100 µl) intramuscularly into the deltoid muscle of the left arm with a BCG scar. The injection site will be covered after 10 minutes with a sterile dressing that will be removed at the one-hour observation.
  - **Group 2** (control) will not receive any vaccines.
- The infant and parent will remain at the clinical area for one hour following vaccination and will then be allowed to return home.
- The injection site will be inspected at 10 minutes when a dressing will be applied.
- Vital signs will be checked at 30 minutes (+/- 5 min) and 1 hour (+/-10 min) post injection.
- At 1 hour (+/-10 min) the dressing will be removed and discarded. The largest diameter of any induration or redness and any other local reaction at 1 hour will be documented into the CRF. An assessment for possible systemic adverse events (AE's) will be carried out and documented on the CRF, and any concomitant medication documented.
- A nurse / field worker will visit subjects at home daily for the first two days after MVA.HIVA vaccination to record safety and reactogenicity data on a standard CRF form.

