## **CONFIDENTIAL**

Minimum details to be given in a telephone report are:

- Name of reporting doctor and contact telephone number.
- Study number.
- Nature of adverse event.
- Subject details (number, initials, sex, date of birth, weight and age).
- Date and time of event.
- Date and time of MVA.HIVA administration and dose.
- Other drug history.
- Other relevant history.
- Outcome.
- Causality.

The event will be documented on the SAE page of the CRF and reported to the Sponsor, Local Safety Monitor, DMEC, relevant Ethics Committees, Gambia Medicines Board, TSC, collaborators and funding agency as appropriate.

After the local ethics committee's response to the SAE report is received, the Sponsor, Principal Investigator, Local Safety Monitor and available co-investigators will communicate to determine the future plan for the study, which could involve amending the protocol, discontinuing the vaccinations, or continuing unchanged for the other volunteers.

**A suspected unexpected serious adverse reaction (SUSAR)** is different from an SAE in that it is unexpected and thought to be related to the study vaccine. If an unexpected adverse reaction to the trial vaccine is suspected, the Sponsor will comply with the regulatory requirements on reporting SUSARs.

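### The automatic SUSAR hold (Protocol 9.3) lifts when a safety review is convened, not completed, and is not tied to the 9.2 continuation decision, which does not require the DMEC's recommendation: a minor, cheap wording fix

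*Protocol*

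**What the plan says.** Protocol 9.3, Halting Rules, contains one automatic hold: "Any SUSAR will result in suspension of the trial until a safety review is convened". It does not say who conducts the review, whether it must reach a conclusion, or who authorises restart.

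Protocol 9.2, Serious Adverse Event (SAE) Reporting, describes what follows an SAE report. Once the local ethics committee has responded, "the Sponsor, Principal Investigator, Local Safety Monitor and available co-investigators will communicate to determine the future plan for the study". The options named are "amending the protocol, discontinuing the vaccinations, or continuing unchanged for the other volunteers". The DMEC is not in that group. It is on the list of those to whom the event is reported, a list qualified by the words *as appropriate*.

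The protocol does give the DMEC a role in safety review. Section 9.3 says: "The DMEC will be appointed to review relevant safety information and all Serious Adverse Events". The sponsor also delegates to it the "right to temporarily suspend or prematurely discontinue this trial at any time and for any reason as described in the DMEC charter". For the Local Safety Monitor (LSM), who reviews SAEs as they occur, 9.3 says: "The LSM has the power to suspend enrolment into the study if deemed necessary following an SAE".

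**The concern.** A hold after a suspected unexpected serious reaction exists so that someone can judge the event before the next participant is exposed. A hold that ends when the reviewers are called together secures a meeting but not its conclusion. This is the only automatic hold in the protocol, and the recipients are healthy infants who are not expected to benefit directly. The DMEC is already appointed to review every SAE, yet nothing in the protocol makes its conclusion a condition for resuming. If the hold lapses, the DMEC has to act to bring it back. The safer default is that vaccination stays stopped until the review is done.

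**Working it through.** The check is mainly textual. The protocol gives no figure of its own on this point to reproduce.

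**1. What ends the hold, and what governs the decision to continue**

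| Element | Protocol 9.3, Halting Rules | Protocol 9.2, SAE Reporting |
|---|---|---|
| Trigger | Any SUSAR | Any SAE, so every SUSAR too |
| Stops vaccination automatically? | Yes | No |
| Event that ends the step | Safety review convened | Future plan decided |
| Local ethics committee's response required first? | Not stated | Yes |
| DMEC recommendation required? | Not stated | Not stated |
| Refers to the other section? | No | No |

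The section that stops vaccination has the weak end point. The section with the outside gate does not stop vaccination.

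**2. Can the hold end before the ethics gate operates?** Section 9.2 gives these times, counted from the day the investigator becomes aware of the event:

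- report to the sponsor and LSM: within one working day (24 hours);
- report of an unexpected related SAE to the ethics committees: within 15 calendar days, or 7 if fatal or life-threatening;
- ethics committee's response: no time given;
- safety review under 9.3: no time given, either for convening or for completion.

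A review convened before day 15 (or day 7) could therefore precede even the report to the ethics committee. On the wording of 9.3 the hold would then be over, and 9.2 contains nothing that keeps vaccination stopped.

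**3. How many infants could be affected?** Inputs: one dose in each of 24 infants (4.1). If m infants have been vaccinated when the hold begins, the number still to be dosed is 24 − m:

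- m = 1: 24 − 1 = 23
- m = 12: 24 − 12 = 12
- m = 24: 24 − 24 = 0

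This counts infants not yet dosed. It does not count exposures in the gap, which would need an accrual rate and a review time that the protocol does not give.

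**4. What would a longer pause cost?** Input: Visit 3 takes place at 20 weeks ± 10 days (6.2).

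- 20 weeks = 20 × 7 = 140 days, so permitted ages run from 140 − 10 = 130 to 140 + 10 = 150 days.
- Width from first to last permitted day: 150 − 130 = 20 days.
- An infant exactly 20 weeks old when the pause starts has 150 − 140 = 10 days left, so a pause of more than 10 days loses that infant.
- A pause of more than 20 days loses every infant who was inside the window when it started.

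Randomisation takes place at Visit 3, so the infants lost would have been consented and bled but not yet allocated.

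**The case against.** The strongest reply is that an outside gate already exists. The sentence in 9.2 on the future plan opens with the local ethics committee's response as a precondition. A SUSAR is an SAE, so that precondition applies, and under 9.3 the joint ethics committee may itself discontinue the trial. A reader might infer that the trial team alone could decide to carry on with no outside view. The documents do not support that. What remains is narrower: the ethics gate applies to the decision on the future plan, not to vaccination in the meantime, and 9.3 does not point to it.

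Second, *convened* may simply mean *held*, and 9.2 treats continuing as something still to be decided. This is plausible. It is why the point concerns wording, and why 9.2 and 9.3 should not be read as contradicting each other.

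Third, the DMEC and LSM can both intervene. The DMEC reviews all SAEs and may suspend or stop the trial. The LSM reviews SAEs at once, may suspend enrolment and takes part in the 9.2 decision. These are real safeguards, and it would be wrong to infer that the DMEC has no role. But they are discretionary powers to stop, not a condition for resuming.

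Fourth, 9.3 leaves DMEC procedures to a charter that is not shown and may already set restart conditions. This stands. The point concerns what the protocol itself requires. If the charter does cover restart, the protocol's sentence should match it.

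**Conclusion.** The point holds as a minor improvement. Section 9.3 ends the SUSAR hold at the convening of a review and does not link it to 9.2. Section 9.2 makes continuation wait for the local ethics committee's response but not for the DMEC's recommendation, and it does not stop vaccination meanwhile. Read literally, dosing could resume before the review concludes.

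The size of the gap cannot be given. Up to 23 doses could remain when a hold begins, but the number given during the gap is unknown. The conclusion assumes the literal meaning of *convened* and a charter that does not already make completed DMEC review a condition of restart. If either assumption fails, the change only makes explicit what was intended. A reader might go further and infer an unsafe trial or a missing independent review. The text supports neither, given the ethics response and the suspension powers.

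**What to change.** In 9.3, Halting Rules, keep the statement that any SUSAR suspends the trial, delete the clause about convening a review, and add: *No further infant will be vaccinated until the safety review, including the DMEC's review, is completed and a documented decision to resume has been taken under section 9.2.*

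In 9.2, add that the decision on the future plan is taken after receiving the DMEC's recommendation as well as the ethics committee's response already required there. Both sections then set the same gate for the same restart. Check that the DMEC charter agrees.

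The cost is one sentence, one clause and a check of the charter. No new committee or data are needed, and the sample size and analyses do not change. The downside is a possibly longer pause after a rare event, because the protocol sets no deadline for the ethics response or the DMEC review. Some infants may pass the 20 weeks ± 10 days window, including all of those already inside it if the pause exceeds 20 days.
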